### Retention and adherence

Important retention and adherence strategies include contacting participants for data collection and to update contact information every 6 months. We will send electronic birthday cards and birthday wishes via e-mail and text message. We will also obtain participants’ addresses and telephone numbers and 3 other secondary contacts to allow us to track them during the 24-month study. We give incentives to motivate individuals to enroll in the study, maintain interest, and sustain participation for the 24-months of e-Book or CHOICES. All participants receive $20 for visits 1–4 as a small stipend for their time and to cover Internet access costs. We will also offer $30 for providing confirmation of their SCD or SCT status. At the 24-mo study visit, we will offer an incentive bonus of $40 for completing the 5th study visit; total stipend/incentive is $150 per participant, the same amount offered in our previous studies. Over 5 visits, participants are expected to take 230 minutes (3.8 hour) on average to complete the entire study over 24 months. We will make every effort possible to minimize participant burden. In addition to the above incentives, we will use other general study procedures including: (1) texting, e-mailing, or calling participants to remind them that a study visit is due and to remind them when the visit window closes; and (2) updating contact addresses and phone numbers at each contact. In the pilot study, we contacted participants via text messages and social media platforms, a process that proved very effective for retention. We have ample evidence that these procedures enhance retention and result in low attrition and missing data rates, which leads to high study protocol adherence.

### Competition with other trials

As an innovative and unique reproductive health behavior trial, we expect that few other trials will pose potential competition. Our community-based recruitment plan, which was effective in our prior study, also minimizes this potential threat to our success.

### Available population

At UF, the UF Health Shands Hospital serves approximately 540 patients with SCD and the UF Health Jacksonville Hospital serves approximately 393 patients with SCD; 933 total patients with SCD. With an estimated 2019 population of 21.5 million that is 16% Black or African American, it is not surprising that Florida has a large population of patients with SCD, estimated at 8,374 to 14,236. Since we will recruit from across the U.S. for this Internet-based study, the available population of 100,000 individuals with SCD is more than adequate to meet our accrual goal of 506 recruited and 430 completed participants. Based on attrition in our prior community-based studies of adults with SCD or SCT, we will recruit 506 participants. With a projected 15% attrition rate, we expect 430 participants to complete the study.

### Sample power

Aim 1. In our 2-year longitudinal trial, the CHOICES group had an average knowledge score of 12.0 ± 3.0 and the e-Book group had an average knowledge score of 11.1 ± 3.1 at the end of the study. Based on this finding, the proposed sample of 430 can detect the intervention effect on participants’ knowledge (primary outcome) with a power of 85%. In our exploratory analysis of at-risk participants wanting to be pregnant soon and avoid having a child with SCD, those in the CHOICES group were at risk 30% ± 37% of the time and those in the e-Book group were at risk 41% ± 44% of the time. Based on this preliminary finding, we estimated that the proposed study sample of 430 will provide 80% power to detect the intervention effect on the secondary outcome (time at-risk) with a two-sided Type I error rate of 0.05. Aim 2. The subgroup analysis proposed for Aim 2 is exploratory in nature. Our study is not powered to detect difference in knowledge and behavior outcomes between demographic groups or acceptability groups.

#### Participant participation duration

The duration of study participation is 24 months. The participant’s flow of study activities appear in Fig 2.

### Procedures

The RS will develop Facebook pages for the study recruitment and retention processes. We will provide the potential participants with a link to the study website where they complete screening questions. RS receives confirmation of eligibility and sets up a time to discuss consent. Participants are sent a link to sign an online consent form, and have questions answered by the RS, who directs them to provide verification of SCD or SCT status. Once the RS receives the verification and approves the participants for participation, RS registers participants and participants are prompted to create a login and password on the CHOICES website. The software application randomizes the participants based on registration information after verified by the RS. The participants complete baseline measures and receive the CHOICES or e-Book based on group assignment. Table 1 lists a summary of the study data collection and intervention points, including boosters at 6 and 12 months and nudges monthly during the first 12 months of the study. For all intervention sessions, the experimental group reads or listens to the CHOICES intervention and the control group reads or listens to the usual care materials (e-Book) on the computer or mobile devices. At each follow-up visit, participants enter data with the SCKnowIQ data collection app (Table 1). Participants receive payments after each verified task via their selected method (mail, digital).

**Table 1 pone.0294907.t001:** CHOICES sickle cell study data collection and intervention summary.

Study Event	Time Points (mo)					
	Baseline	Posttest	6	12	18	24
**SCKnowIQ** Computerized Questionnaires—Sickle Cell:						
**Knowledge** Questionnaire	X	X	X	X	X	X
**Behavior** Tool	X	X	X	X	X	X
Demographic Questionnaire	X					
Intervention Acceptability		X				X
**CHOICES**—**Intervention** X initial; O nudges and booster tailored to most recent responses	X		O	O		
**e-Book**—**Intervention** X initial	X					
**Computer Acceptability Scale**		X				X

### Intervention

We created **CHOICES** (Fig 3), an innovative web-based software application to provide interactive information about SCD, its genetic inheritance, and reproductive health options for individuals with SCD or SCT. CHOICES is a multimedia intervention that provides targeted and tailored information for participants to overcome their misconceptions about their reproductive health options. Targeted to their gender and tailored to their knowledge, behavior during the previous 6 months, and parenting plan (i.e., intention to have child with SCD or not within the next 6 months), CHOICES presents information about options to help the participant achieve their parenting plan through reproductive partner selection based on sickle cell status, prenatal testing, ovum and sperm donation, advanced reproductive technologies, and options to avoid pregnancy or adopt, as well as information related to risks of pregnancy in the woman with SCD. The website will be housed on secure UF servers and accessible via computers or mobile devices (e.g., tablets, smart phones); device capture will inform plans for long-term dissemination.

**Fig 3 pone.0294907.g003:**
[figure not shown]
Examples of CHOICES screens.

We used Kolb’s Experiential Learning Theory (ELT) [19] to organize the presentation of the CHOICES intervention material (Fig 3) and behavior concepts to frame the content. All the materials are written at an 8^th^ grade level and based on evidence or best-practice facts or scripts for reproductive health in young adults with SCD or SCT. The facts or scripts in the booster intervention delivered at 6 months and 12 months are tailored to the participant’s knowledge gap. We will modify the booster to focus more on the participant’s risk behaviors that are not consistent with the current parenting plan and use nudges toward actualization of the concordant behavior that is needed to implement the parenting plan. The participant’s responses on SCKnowIQ govern the specific health and behavior information provided in the booster and the participant’s responses on the update queries associated with the nudges, which will be developed in the proposed study.

Specifically, the CHOICES program reads the SCKnowIQ database for evidence of knowledge deficits about genetic inheritance of SCD and behaviors in the previous 1–6 months that are inconsistent with their parenting plan. CHOICES then presents information to target the knowledge gap and will be expanded to provide behavior guidelines, options, and role model nudges that help the participant implement the parenting plan, including any change in the parenting plan during the study. CHOICES respects the participant’s parenting plan decision (there is no correct parenting plan other than the one the participant wants) and provides information about behaviors needed to enact the parenting plan. For this RCT, only participants stating they want to avoid having a child with SCD (their parenting plan at baseline) will be included, but based on the preliminary study at baseline, >90% reported this parenting plan and it was stable over 24-months.

The CHOICES program provides text, video clips, audio clips, graphics, cartoons, photos, and animations to help the participants overcome their knowledge gaps about SCD inheritance, available reproductive options, and state or role model the behavior steps to be taken to implement their parenting plans. There are extensive video clips of couples discussing their reproductive health choices to role model behaviors needed to implement their parenting plan, and how they feel about their choices and behaviors. For example, in one clip, a young couple breaks up after the young woman discloses that she has SCT and learns that her boyfriend also has SCT; she breaks up with him because she does not want any risk of having a baby with SCD and she would not consider other reproductive options, such as advanced reproductive technologies or pregnancy termination, particularly since she wants a large family. Another couple discusses being adoptive parents because they do not want to risk the woman’s health given that she has SCD. Video clips of these and other diverse scenarios bring reproductive health decisions to life serving to model the behaviors needed to implement the parenting plans and to supplement the text information. CHOICES includes skills training to promote mastery in performing the behavioral steps needed to implement the parenting plan, such as talking to one’s partner, getting tested for SCT, determining risk given a couple’s SCT or SCD status, selecting appropriate birth control methods, and adopting/fostering a child.

Therefore, the intervention is based on ELT to provide engaging and experience-based learning that also includes key elements important for concordant behavior. We will strengthen the behavioral component in the proposed study by adding reinforcement nudges and additional skills mastery components to the booster sessions. These additions will provide opportunities for skill development regarding concordant behavior that are needed to implement the parenting plan but were not performed in the previous 1–6 months. Boosters will also include positive reinforcement statements to recognize the participant’s concordant behavior successes and encouragement for success and importance for concordant behavior. Participants completed the intervention in 71.8 ± 28.7 minutes; each booster in 8 minutes, which will be longer with the refinements that we plan to add based on preliminary findings.

The e-Book intervention contains information typically shared in clinical SCD care. It does not include other information related to the SCKnowIQ knowledge items or any of the behaviors needed to implement a parenting plan. The e-Book intervention will not include booster sessions, which differs from the preliminary study to minimize the repetition of genetic inheritance information, a key element of the CHOICES intervention. Although not as lengthy as CHOICES, the e-Book was completed at an average of 8.6 ± 2.8 minutes at baseline. It is sufficiently long, attractive, and engaging to retain participants randomized to the usual care control group; key factors for an adequate control condition. Interestingly, during the preliminary study and in interviews after the study, many e-Book participants commented that they were pleased to be assigned to the intervention group (even though they were not), which indicates that the control condition is sufficient for its intent—2-year longitudinal retention of the sample. Also, human contact is the same for both groups, and the time-on-task on the computer is unlikely to influence study knowledge and behavior endpoints.

### Acceptability of interventions

At the conclusion of the preliminary study’s immediate posttest, participants in both groups were prompted by the computer to indicate what it was like to participate in the study and what they thought about the intervention program (Usability and Acceptability Instrument). Overall, they gave positive responses that included “great learning experience,” “great program,” “interesting,” “helpful,” and “informative.” Although a few of the participants in the e-Book group saw the content as a “refresher,” most participants in both groups found the content new and beneficial to their understanding and learning. Some of the participants went beyond focusing on their own learning and noted that the information would help stimulate awareness about SCD and SCT in individuals and communities. More of the CHOICES group than the e-Book group indicated that they “enjoyed” the learning and liked the various ways it was delivered including the presentation of the videos. Some participants clearly indicated that the computer was an easy, convenient, and “wonderful” way to convey this important information. As one participant said, “It beats classroom learning!” No negative comments were given about the use of computers. There were some suggestions about computer use, such as how to navigate the touch screen and desire to complete it at home on their own personal computers.

#### Manipulation check for the fidelity of the usual care and CHOICES interventions

Two assessments are made as intervention manipulation checks: 1) the delivery of the intervention (usual care e-Book or CHOICES) to participants and 2) the participant’s take of the intervention. The manipulation check of the intervention delivery is assessed by calculating ratios for the number of intervention elements available to the participants and the actual number of intervention elements viewed by the participants. It is expected that this ratio will be 1 for most participants, indicating that they reviewed all the elements available to them. The ‘take of the intervention’ is measured by the gain in knowledge (study endpoint).

### Measures

We measure study process, outcome, descriptive and exploratory variables using a computer-based instrument that we named SCKnowIQ. SCKnowIQ includes items from previously validated instruments, items adapted from instruments that have been used in published population-based studies, and new items generated to measure concepts for which we were not able to find validated tools (Table 2). All instrument items were validated for the SCD and SCT populations and tested for reliability in the preliminary studies. The iterative methods used in the think aloud study with 20 participants produced valid study measures that are also reliable [16]. In total, participants take about 25 minutes to complete the measures at each time point. Items allow those not sexually active to give meaningful answers. Table 2 includes the validity and reliability information for each tool.

**Table 2 pone.0294907.t002:** SCKnowIQ computer data collection tool.

Concept Measured	Instrument Name	# Items	Internal Consistency	Test/Retest Reliability	Original Tool References
** *Participant Outcome Variables* **					
SC Knowledge Reproductive Knowledge	SC Reproductive Knowledge Questionnaire	17	.78	.72	Adapted from [20, 21, 24, 25] Validated in SCD/SCT [16]
Behaviors	Behavior Questionnaire	8	Not applicable (NA)	NA	Adapted from^:^ [20, 21, 26] Validated in SCD/SCT [16]
** *Descriptive & Exploratory Variables* **					
Demographic Characteristics	Demographic Questionnaire	29	NA	NA	Validated in SCD/SCT [16]
Acceptability	Usability and Acceptability Instrument	20	NA	NA	Validated in SCD/SCT [16]

#### Participant outcomes

The SCKnowIQ tool includes 71 items, with many that are sex/gender specific [16]. The SCKnowIQ is a web-based app that was programmed based on many years of experience and a background in both current programming strategies and statistics. During the app’s design and development, its usability was of high priority to avoid extraneous variability caused by users’ differing experience with computers and their disparate physical and cognitive functions, which could contribute to increased measurement errors. A thorough usability test was conducted in the target population, and a few web pages were modified or improved by test outcomes [16]. We include managerial measures to ensure the data validity such as making sure that participants input data on time to avoid missing data or to ensure that data are collected on time.

#### Knowledge

The *Sickle Cell Reproductive Knowledge Questionnaire* portion of the SCKnowIQ measures knowledge of the genetic transmission of SCD and SCT, etiology of SCD, parenting options for people with SCD or SCT, types of contraceptives safe for people with SCD or SCT, and risks of complications during pregnancy for the woman with SCD. Responses are multiple choice options. Scores are totaled across all items, ranging from 0 to 17; higher scores reflect better knowledge than lower scores. Other details appear in Table 2.

#### Behavior: *At-risk* time

The *Behavior Questionnaire* is an 30-item, sex/gender-specific measure of reproductive health behavior relevant to people with SCD or SCT [20, 21]. The items are part of the SCKnowIQ and focus on behaviors and outcomes during the past 6 months relevant to the success of their parenting plan: a) partner’s sickle cell status; b) use of contraceptive methods; c) use of advanced reproductive technologies such as in vitro fertilization (IVF); d) pregnancy; e) use and outcome of prenatal testing; f) pregnancy outcome (e.g., pregnancy-induced changes, abortion, miscarriage, birth of an infant with SCD, birth of an infant unaffected by SCD or SCT, birth of an infant who is a carrier of SCT). The *at-risk* time of each participant during the 24-mo study will be obtained by aggregating the at-risk status outcomes of all visits. Based on their answers to the behavior questions (a-f) at each visit, we will assess whether they are at risk in the previous six months. A person is considered not at risk if their behaviors meet any of the following criteria: 1) their partner has Hgb A; 2) they always use effective birth control methods; 3) they use prenatal testing or advanced reproductive technology to ensure the baby is free of SCD (otherwise, a person will be considered *at risk*). The behavior items (f) will also allow us to calculate the number of children born during the study for descriptive purposes. The logical compatibility between behavior items and demographic items (SC status, number of children, etc.) in the same visit and across multiple visits of our previous studies and the participants’ responses to cognitive interviews in the preliminary study [16] attest to their validity. Since all participants will be at risk at baseline, the posttest *at-risk* score ranges from 0% of the time at risk to 100% of the time at risk across the 4 posttest measures after the baseline visit.

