### Screening and consent

As an Internet-based study, all screening and consent processes are completed via the website to which the individual is directed to all the recruitment materials. The individual completes the screening questions, reads the online consent form, calls a number to discuss questions with a qualified staff member, and signs the consent by typing his/her name and clicking a statement of consent. Before the individual is randomized, however, we require the research specialist (RS) to speak to the consenting person via a phone call and upload of an official healthcare record documenting SCD or SCT status. The RS who will assist individuals in these screening and consent processes will be trained in Good Clinical Practices for research and IRB and HIPAA procedures. The training includes role-play and retraining if the staff makes mistakes in the process(es).

Safeguards for pregnant women who are not a targeted population (participants could be pregnant on enrollment or during the study), include a behavioral intervention with important information related to reproductive health decisions. Therefore, risks to pregnant women are minimal, and no greater than what they might face from daily life.

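### Read literally, the at-risk scoring rule counts a six-month window with no partner or no intercourse, and no contraception, as time at risk

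*Protocol article*

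**What the plan says.** The section on at-risk time (Measures, Behavior) classifies each participant at each visit for the preceding six months and aggregates the four follow-up classifications into a score from 0% to 100%. There are three routes out of the at-risk state. The rule opens with the partner's status: "A person is considered not at risk if their behaviors meet any of the following criteria: 1) their partner has Hgb A". The second route is uninterrupted use of effective contraception. The third is prenatal testing or assisted reproduction aimed at an unaffected baby. All remaining windows fall to a default, introduced by the words "otherwise, a person will be considered", which assigns them to the risk category. Neither absence of a partner nor absence of intercourse is mentioned.

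Other parts of the article show that such participants are expected. The Measures section says of the questionnaire: "Items allow those not sexually active to give meaningful answers". The Intervention section lists, among the content of CHOICES, "options to avoid pregnancy or adopt", and describes a video clip in which "a young couple breaks up after the young woman discloses that she has SCT and learns that her boyfriend also has SCT". The Eligibility criteria require the ability and intention to conceive and being at risk, but not a current partner.

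The Sample power section gives pilot at-risk time of 30% ± 37% (CHOICES) and 41% ± 44% (e-Book), and claims 80% power with 430 participants at a two-sided 0.05 level.

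**The concern.** The first criterion presupposes a partner, the second the use of contraception, and the third a pregnancy or a medically assisted attempt at one. Someone who is single or abstinent and uses no contraception meets none of them, so the default applies. That person cannot conceive a child with SCD in that window, yet the window is scored the same as unprotected intercourse with a partner who has the trait.

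Two things are at stake. First, the endpoint does not measure what its name says: at-risk time is overstated in both arms. Second, the misclassification may depend on treatment. CHOICES teaches partner selection and ways to avoid pregnancy, and it models leaving a partner who carries the trait; the e-Book omits the behaviors needed to carry out a parenting plan. If CHOICES leads more people to spend time without a partner or without intercourse, those windows count against it. At-risk behavior is the only secondary endpoint in Aim 1, and the trial was restricted to at-risk participants because the preceding study found no behavior effect.

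**Working it through.** **1. Cases put through the rule**

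| Participant's window | Criterion met | Score | Can a child with SCD be conceived or carried? |
|---|---|---|---|
| No partner, no intercourse, no contraception | none | at risk | no |
| Partner with SCT, abstinent throughout, no contraception | none | at risk | no |
| Left a partner with SCT before the window, single throughout, no intercourse or contraception | none | at risk | no |
| Single, always uses effective birth control | 2 | not at risk | no |
| Pregnant, partner has Hb A | 1 | not at risk | no |
| Pregnant, qualifying prenatal testing or reproductive technology | 3 | not at risk | handled by the rule |
| Pregnant by a partner with SCT or SCD, neither testing nor technology | none | at risk | yes |

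Only the first three rows are misclassified. If abstinence were counted as a birth control method, those rows would meet criterion 2; the text does not say so.

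**2. The plan's own power figure**

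Inputs (Sample power): difference 41 − 30 = 11 points; SDs 37 and 44; 430 participants, taken as 215 per arm (two arms, blocks of four).

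- Pooled SD = √((37² + 44²)/2) = 40.65
- Standard error = 40.65 × √(2/215) = 3.92
- Power = Φ(11/3.92 − 1.96) = 80.1% (79.9% with the noncentral t)

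The stated 80% reproduces.

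**3. How misclassified windows enter the difference**

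Let mE and mC be the percentages of all windows in e-Book and CHOICES that carry no exposure but are scored at risk. Each arm's observed mean is its correctly scored mean plus m, so

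observed difference = correctly scored difference + (mE − mC).

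Equal percentages raise both arms' levels and leave the difference unchanged. Each point by which mC exceeds mE removes one point.

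**4. Illustration**

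Assumptions: the correctly scored difference is 11 points, the SD stays at 40.65, and there are 215 per arm. The excess is an assumed range; the documents give no value.

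| Excess mC − mE (points) | Observed difference | Power |
|---|---|---|
| 0 | 11 | 80.1% |
| 1 | 10 | 72.3% |
| 2 | 9 | 63.1% |
| 3 | 8 | 53.2% |
| 5 | 6 | 33.4% |

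For scale: with complete data each arm has 215 × 4 = 860 follow-up windows, so a 2-point excess is about 17 windows (0.02 × 860) and a 5-point excess is 43.

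**5. A variant with the same rate of error in both arms**

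If the same fraction q of truly not-at-risk time is misclassified in each arm, the means become 30 + 70q and 41 + 59q, and the difference is 11(1 − q). With the SD held, q = 10% gives 9.9 points and 71.4% power, and q = 20% gives 8.8 points and 61.2%. If the SD shrank in the same proportion, power would stay at 80.1%. The loss therefore depends on assumptions that the documents cannot settle.

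**The case against.** The case for leaving the rule alone has several parts.

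- *An article condenses.* Item-level coding may sit in a fuller document, and abstinence may be meant under criterion 2. This has some weight, but the article does more than stay silent: it states the algorithm and a default for everyone left over. A programmer following it would score these windows at risk.
- *Eligibility limits the problem.* Participants must intend to conceive and be at risk, which should reduce time spent single or abstinent. This stands as a reason why the share may be small. It does not make the share zero, since no current partner is required and the questionnaire provides for people who are not sexually active.
- *The power may be unaffected.* If the pilot values were scored by this same rule, any misclassification is already inside the 11 points and the 80% stands. This is correct, and it is why the losses above are illustrations only.
- *The endpoint is secondary and the bias conservative.* Success is judged on knowledge, and the plausible direction is against CHOICES. Both are true. They limit the consequence but do not remove the misclassification.

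Three stronger readings are tempting and not supported. A reader might infer that everyone without a partner is scored at risk; a single participant who always uses effective birth control meets criterion 2. A reader might infer that pregnant participants are scored wrongly as well, since "participants could be pregnant on enrollment or during the study". Criteria 1 and 3 already cover the qualifying pregnancies, and an untested pregnancy with a partner who has SCT or SCD is a real exposure. Treating all pregnant windows as unexposed would credit exactly that case. Finally, a reader might take the excess in CHOICES as established. One modelled break-up and the intervention's content make it plausible, but the documents hold no data on it.

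**Conclusion.** The point holds for windows with no partner, or no intercourse, throughout and no contraceptive use. The stated rule scores them at risk although conception is impossible, so at-risk time is overstated in both arms. Whether the comparison between arms is biased depends on whether such windows are more frequent under CHOICES; if they are, the bias runs against CHOICES, one point for each point of excess.

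The size cannot be fixed from the documents. The figures of about 63% and 33% power for excesses of 2 and 5 points assume a correctly scored difference of 11 points, an unchanged SD of 40.65 and 215 per arm. The planned 80% is right on its own inputs, and stands if the pilot used the same rule. The primary endpoint, knowledge, is not touched.

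**What to change.** Before any unblinded analysis:

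1. Add a fourth not-at-risk criterion to the scoring rule: no partner, or no intercourse that could lead to conception, throughout the six-month window. State that abstinence is counted here, so that nobody has to guess whether it falls under criterion 2.
2. Score it from the existing SCKnowIQ answers, which already let people who are not sexually active respond.
3. Apply the same rule to at-risk status at baseline, and revise the statement that all participants start at risk if it no longer holds. Everyone randomized stays in the intention-to-treat analysis.
4. Leave pregnancies to criteria 1 and 3 as now.
5. Establish whether the pilot's 30% and 41% were scored by the present rule. Rescore them under the amended rule and restate the 80% power if the values change.

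The cost is one sentence in the rule, a small change to the scoring code and a rescoring of pilot data. No new items or visits are needed. The change is credible only if made before results by arm are seen.
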